#### Serological survey—design and methods

While the facility-based fever surveillance studies provide estimates of the burden of medically attended dengue disease, evaluation of all DENV infections in a population—including subclinical and mildly symptomatic infections, which impact immune status—is needed to capture the overall impact of dengue. As part of the study package, population-based serological surveys were conducted in the same catchment population used for the fever surveillance. At each of the three sites in Africa, the serosurvey was conducted on a cohort of approximately 3000 randomly selected residents of urban and semiurban parts of Ouagadougou, Lambaréné and Mombasa. Without individual-level census information on all residents of Lambaréné and Mombasa, with help of community/village health workers, randomisation was done based on neighbourhoods (or defined areas for which the health workers/volunteers are responsible) as cluster units. As the community/village health workers are familiar with the villages and their residents, they are good entry points into the communities. With these health workers, the field team screened houses in the selected villages by knocking on doors of every 5–7 houses, depending on the household density per neighbourhood. Also, demographic information collected in previous research projects conducted in the same area was used as a guide, if available. In the case of the site in Ouagadougou, HDSS data were available and the EQUITE SANTE, a CIHR funded research programme of the University of Montreal, had set up a geographic information system database of houses in the study area. Using these data, households of potential enrolees of the serosurvey were preselected randomly and household visits were made in Ouagadougou. In the three sites, about 45% of the serosurvey samples were targeted to be collected from children 1 to 14 years of age, and 55% were targeted to be collected from adults between 15 and 55 years of age to reflect the age distribution of the general population of the area. Household-based enrolment was offered to the head of the household until the specific cap for the age-group was reached in Lambaréné and Mombasa.

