Randomly selected subjects 1–55 years of age underwent phlebotomy (5 mL for children and 7 mL for adults) twice—before the rainy season and after the rainy season, at approximately 6-month intervals. The sera were evaluated using IgG indirect ELISA at baseline and after 6 months. The presence of dengue IgG antibodies at 6-month intervals will be used to estimate the level of occurrence of inapparent DENV infection and to calculate the rate of infection in the catchment population. Flow cytometry-based DENV neutralisation assays will be applied to a subset of samples to assess for presence of dengue neutralising antibodies and seroconversion over the 6-month interval. In addition to overall seroconversion, age-specific seroconversion estimates in the catchment population as well as the proportion of inapparent infections will be determined.

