As outpatient disease accounts for the greater part of dengue disease burden, clinical profile of individuals with DENV infection will be characterised by the type of treatment (hospitalised vs outpatients) as well as by severity of the disease (severe vs non-severe by the 2009 WHO criteria).^46^ Classification is determined after the course of illness is completed (typically during the convalescent visit). Symptomatic dengue is classified as outpatient or hospitalised. Progression of dengue is recorded as DF, DHF I, DHF II, DHF III or DHF IV, and clinical patterns will be compared by the severity grade.^46 47^ These will be compared with results obtained from other DVI studies in Latin America (Colombia) and Asia (Thailand, Vietnam and Cambodia). Overall, comparisons will be made across Burkina Faso, Gabon and Kenya.

With the age-stratified sera that reflect the age distribution of the general population of the country, the serological survey sampling strategy ensures sufficient subjects to obtain precise age-specific estimates of seropositivity and seroconversion of the catchment area population. The seroconversion rate and change in the immune status will be determined by age group during the study period. The age-stratified serosurvey data will also allow calculation of the force of infection of dengue in the study population. After enrolment, there are subjects who drop out in the follow-up bleeds about 6 months later. Basic demographic information will be compared between those that completed participation and those with incomplete participation to check whether study subjects represent the catchment area population. Comparisons will be made among Burkina Faso, Gabon and Kenya.

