One potential source of bias in estimating the incidence of symptomatic dengue is under-ascertainment due to the community residents with relevant symptoms seeking care from other healthcare providers and facilities than the study facilities. As the study design remains passive surveillance, cases are ascertained only at our study facilities. By estimating the proportion of febrile patients seeking care elsewhere as well as refusal rates among the potential enrolees that were screened for eligibility criteria, the degree of febrile patients missed by the study can be determined. Inverse probability weighting will be used to account for these potential subjects missed by the surveillance as adjustments in incidence calculation. Also, depending on the transmission volume of dengue or other cocirculating diseases with onset of fever, there may be patients that are diagnosed with other diseases and ruled out for dengue. Furthermore, with respect to dengue diagnostics for our serological surveys, there are other circulating flaviviruses in Africa leading to challenges in identifying antibodies to past dengue infections. While our testing plan assesses for some flaviviruses, others known to circulate in Africa, such as Banzi and Usutu viruses, are not part of the testing plan.^48–50^ Due to resource limitations, serological testing will be limited to yellow fever virus, West Nile virus, Zika virus and Japanese Encephalitis virus as well as DENV 1–4. Therefore, in some cases, it may be difficult to determine prior exposure to DENV versus other flaviviruses based on serological data. This cross-reactivity may lead to overestimation of dengue force of infection.

In addition, the serosurvey and healthcare utilisation survey are conducted on a randomised subsample of the catchment area population and there may be limited generalisability of the data collected from these surveys. With unknown differences among those that agree to participate and those that do not agree, the data may not be representative of the general population of the study countries.

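### The serosurvey's completer versus non-completer comparison cannot show representativeness, and it is the only stated response to dropout that affects seroconversion

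*Protocol article*

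**What the plan says.** The serosurvey enrols about 3000 residents per site and bleeds them again at intervals of about six months: one follow-up in Lambaréné and Mombasa, three in Ouagadougou. On testing, Serological survey—design and methods states: "The sera were evaluated using IgG indirect ELISA at baseline and after 6 months". The same section sets enrolment targets of 45% aged 1 to 14 and 55% aged 15 to 55, "to reflect the age distribution of the general population of the area".

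Planned statistical analysis names the outputs: "The seroconversion rate and change in the immune status will be determined by age group during the study period". It says the sampling strategy will give "precise age-specific estimates of seropositivity and seroconversion of the catchment area population". It then acknowledges loss: "After enrolment, there are subjects who drop out in the follow-up bleeds about 6 months later". The response follows: "Basic demographic information will be compared between those that completed participation and those with incomplete participation", and the stated purpose is "to check whether study subjects represent the catchment area population".

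For the fever surveillance the article goes further. Planned statistical analysis adjusts the case numerator for febrile cases seen elsewhere and for refusals, and the Discussion adds: "Inverse probability weighting will be used to account for these potential subjects missed by the surveillance".

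**The concern.** The check does not fit its declared purpose. Completers and non-completers are both subsets of the people who enrolled, and no population comparator is named. A reader of the results could take a reassuring table as evidence of representativeness that it does not contain.

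The check also bears on a main output. Seroconversion, change in immune status and the proportion of inapparent infections all depend on repeat bleeds. If people lost between bleeds differ in infection risk from people of the same age who stayed, the completers' rate is not the catchment rate. If loss differs between sites, the planned comparison of Burkina Faso, Gabon and Kenya is affected too. A table of basic demographics would neither correct this nor show how large it is.

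**Working it through.** **Step 1: what the comparison can detect.** Let a characteristic have share p in the catchment population and share q among those enrolled, and let a fraction d drop out regardless of the characteristic.

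- Share among completers: q(1 − d)/(1 − d) = q
- Share among non-completers: qd/d = q
- Difference between the two groups: 0, whatever the value of q − p

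The check passes however far q lies from p. It tests whether attrition is related to the characteristic. Representativeness requires comparing q, and the completers' share, with p.

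**Step 2: whether another section supplies the missing comparator or a correction.**

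| Component | Selection problem acknowledged | Stated response |
|---|---|---|
| Fever surveillance | Care sought elsewhere; refusal | Numerator adjusted; inverse probability weighting |
| Serosurvey, enrolment | Agreement versus refusal (Discussion) | Listed as a limitation; age targets in two bands |
| Serosurvey, between bleeds | Dropout (Planned statistical analysis) | Demographic comparison of completers and non-completers only |

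The age targets control two broad bands at enrolment. They do not control sex, area or who returns. The limitation in the Discussion concerns refusal, not loss between bleeds.

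**Step 3: illustrative size.** The article gives neither a dropout rate nor a seroconversion risk, so there is no figure of its own to reproduce. All inputs here are assumptions, apart from the 3000 per site, which is taken as stated. With dropout d and risk ratio RR (dropouts to completers, within an age group), the relative error of an unadjusted completers-only estimate is

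1/(1 − d + d × RR) − 1

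| Assumed d | RR = 0.5 | RR = 2 |
|---|---|---|
| 10% | 1/0.95 − 1 = +5% | 1/1.10 − 1 = −9% |
| 20% | 1/0.90 − 1 = +11% | 1/1.20 − 1 = −17% |
| 30% | 1/0.85 − 1 = +18% | 1/1.30 − 1 = −23% |

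To set this against sampling error, assume a completer risk of 5%, d = 20% and RR = 2. The true risk is 0.8 × 5% + 0.2 × 10% = 6.0%, a gap of 1.0 percentage point. With 3000 × 0.8 = 2400 completers, the 95% half-width under simple random sampling is 1.96 × √(0.05 × 0.95/2400) = 0.9 point. Under these assumptions the bias is about as large as the site-level half-width. Clustering, restriction to baseline seronegatives and splitting by age would all widen the interval.

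**The case against.** The strongest reply is that comparing completers with non-completers is the standard attrition check, that enrolment representativeness is handled by random selection and age targets, and that treatment of missing bleeds normally belongs in an analysis plan that is not shown. Much of this stands. The comparison is worth keeping, and the absence of a stated weighting method would be a weak point on its own. It does not answer the mismatch: the article itself assigns the comparison a purpose it cannot serve, and that is stated text rather than silence.

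Four other objections limit the point:

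- Estimates are planned by age group, so loss that differs only by age does not bias the age-specific rates. The risk ratios above must be read as differences within an age group.
- Among baseline seronegatives the baseline IgG result is constant, so it cannot act as a weighting variable for seroconversion in the usual sense. It is useful in the attrition table and for change in immune status.
- The article does not define basic demographic information. Table 1 places address alongside demographic items on the surveillance form, so location may already be intended. Naming it would settle this.
- Weighting for care sought elsewhere or refusal addresses a different selection problem from attrition. It shows that the method is within the team's plans, not that the article is bound to use it here.

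A reader might also infer that 10% to 30% is planned dropout. It is not: Sample size gives that range as a serosurvey non-response allowance that varies by site. Nor is there support for compounding it over the three follow-up bleeds in Ouagadougou. No rate per bleed is given, an interval estimate needs only two bleeds, and Study area and population describes the HDSS population there as stable, with 4.1% migration.

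**Conclusion.** The point holds in limited form. The stated check cannot establish representativeness of the catchment population, and it is the only response the article states to dropout that it acknowledges. Seroconversion and change in immune status are exposed.

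The size is unknown from the document. On the assumed ranges (10% to 30% dropout, within-age risk in dropouts half or twice that of completers), a completers-only estimate would be off by +5% to +18% or −9% to −23%. If risk does not differ within age groups, the error is zero.

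Two stronger readings are not supported. The article does not say that seroconversion will be computed as though loss were random; it is silent on the method. And dropout does not undermine every serosurvey result: baseline seroprevalence, and force of infection derived from it, rest on the enrolment bleed and are unaffected by later loss.

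**What to change.** 1. **Representativeness.** Compare both enrolled and completing participants with the catchment age distribution, and with sex and area where available. Use the HDSS in Ouagadougou. In Lambaréné and Mombasa use the population distribution already needed for the age-specific incidence denominators.
2. **Attrition.** Keep the completer versus non-completer comparison, call it an attrition check, and add baseline IgG status and neighbourhood. Baseline IgG comes from the enrolment bleed. Neighbourhoods were the sampling clusters in Lambaréné and Mombasa, and houses in the Ouagadougou study area are in a geographic database.
3. **Estimation.** Report seroconversion weighted for completion, using age, sex and neighbourhood among baseline seronegatives, alongside the unweighted estimate. For change in immune status, add baseline IgG to the weights.

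The cost is a little more analysis, mainly of data already collected, and slightly wider intervals. The weights correct only for loss explained by the variables in them, which is a reason to show both estimates.

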### Ethical considerations

To minimise inconvenience of the study to patients, clinicians and nurses were sensitised and trained regarding the study requirements and procedures in order for data collection to be integrated into routine patient care. The clinicians and nurses selected for the study receive coordinated support from study field staff throughout the study process. Written informed consent and assent for participants 7 (13 for Kenya)−17 years of age were obtained from patients by study staff. Study staff go through consent and assent documents for short summary of the disease, detailed description of study procedures and information on reimbursement. Patient data are documented in the study designated office; only the study staff have access to the data that are de-identified. Data are exclusively handled in the study office and stored safely in a protected database in the study office as well as on the DVI main server.

## Discussion

Dengue cases have been detected since the 1960s in Africa, and there has been continued presence of *Aedes* vectors in the continent.^5 7^ However, very few dengue studies have been conducted in Africa, and little evidence is based on population-based studies.^6^ Compared with the volume of evidence from SE Asia and the Americas, there is critical data scarcity on dengue in Africa. Suspicion of substantial dengue burden in Africa is based on limited reports of outbreaks and a handful of seroprevalence studies testing different viruses among samples that likely do not represent the general population. In the three countries selected for our field studies, somewhat more data are available, but are still very limited. In Burkina Faso, a recent observational study conducted in 2013 reported that 8.7% of the febrile patients showed positive results on dengue RDT.^16^ In Gabon, one study suggested minimal DENV circulation in rural areas,^21^ while another study reported 12.3% seroprevalence, by IgG antibodies against dengue, among toddlers 30 months of age in semirural parts of Lambaréné.^20^ In Kenya, about 13% of the individuals in Mombasa have been reported to have evidence of past or current DENV infection by RT-PCR and IgM antidengue ELISA after the 2013 outbreak.^26^ Despite the limited scope and generalisability of these studies, they suggest that there may be more dengue than previously appreciated due to underestimation and misdiagnosis.^25 26^

These studies suggest the presence of dengue and some level of underlying seroprevalence in the countries of our field studies. However, often these studies are limited by their retrospective design or sample collection (blood donors or sample collected from surveys of other diseases) to demonstrate the true, population-based, burden of dengue. We proposed to address this gap by population-based dengue surveillance and seroprevalence studies in West, (West-) Central and East Africa.

The present studies at three sites in Africa will provide important information on undocumented DENV circulation in Africa. Such data will help to strengthen the evidence base for dengue burden in Africa. Better defined disease burden data based on our studies could be used to assess the relative need for dengue prevention and control measures, such as whether a dengue vaccine would be a cost-effective public health intervention for countries in Africa. Clinical findings from our studies could also be used as a guide for dengue case detection and case management.

The studies have some important limitations. We recognise variability of dengue epidemiology over time and by region. Due to resource constraints, our studies are limited in terms of time frames and geographical extent. These constraints may limit the generalisability of our study results.

One potential source of bias in estimating the incidence of symptomatic dengue is under-ascertainment due to the community residents with relevant symptoms seeking care from other healthcare providers and facilities than the study facilities. As the study design remains passive surveillance, cases are ascertained only at our study facilities. By estimating the proportion of febrile patients seeking care elsewhere as well as refusal rates among the potential enrolees that were screened for eligibility criteria, the degree of febrile patients missed by the study can be determined. Inverse probability weighting will be used to account for these potential subjects missed by the surveillance as adjustments in incidence calculation. Also, depending on the transmission volume of dengue or other cocirculating diseases with onset of fever, there may be patients that are diagnosed with other diseases and ruled out for dengue. Furthermore, with respect to dengue diagnostics for our serological surveys, there are other circulating flaviviruses in Africa leading to challenges in identifying antibodies to past dengue infections. While our testing plan assesses for some flaviviruses, others known to circulate in Africa, such as Banzi and Usutu viruses, are not part of the testing plan.^48–50^ Due to resource limitations, serological testing will be limited to yellow fever virus, West Nile virus, Zika virus and Japanese Encephalitis virus as well as DENV 1–4. Therefore, in some cases, it may be difficult to determine prior exposure to DENV versus other flaviviruses based on serological data. This cross-reactivity may lead to overestimation of dengue force of infection.

In addition, the serosurvey and healthcare utilisation survey are conducted on a randomised subsample of the catchment area population and there may be limited generalisability of the data collected from these surveys. With unknown differences among those that agree to participate and those that do not agree, the data may not be representative of the general population of the study countries.

## Conclusion

The data collected from our studies will contribute to the assessment of the unknown dengue disease burden in Burkina Faso, Gabon and Kenya. These data can fill a gap in undocumented burden of dengue in the region and, collectively, may be used to infer dengue burden in other areas of Western, Central and Eastern Africa. Countries in Africa may not consider introduction of a dengue vaccine as a priority in the near future due to many other competing public health problems and limited resources. For cost-effective implementation of public health interventions, accurate data on dengue burden from epidemiological studies would be needed for policy makers to make evidence-based decisions on control and prevention of dengue. Our studies will provide some much needed information based on population-based research to assess dengue burden in Africa.
